### Qualitative evaluation

Success of CDSS interventions is partly dependent on human factors such as user expectations and acceptability, and system usability [30]. Therefore, in order to better understand why MIM+ worked or not afterwards, we also will conduct a qualitative evaluation before and after MiM+ implementation. For this evaluation, a mixed method approach will be used including semi-structured interviews with users, observations of users handling pDDI alerts and a survey among ICU physicians. In Fig. 2, an overview of this study over time can be found.

**Fig. 2 Fig2:**
[figure not shown]
Timeline of different components of this study

### Stepped-wedge design implementation

In our study, each ICU represents one cluster and the MIM+ is rolled-out over nine steps of one month each (see Fig. 3). At each step, one cluster will start with the MIM+. Maximum power for a given number of clusters is achieved when each cluster has its own step [22]. The total duration of the trial is ten months. Whenever an ICU starts with the MIM+, the first month will be considered a pilot month, in which small, local changes to the MiM+ will be allowed. For example, an ICU could argue for the inclusion of an alert for an extra pDDI that was not included in the MiM+ or to discard a pDDI alert from the MiM+. This will be allowed, because the type of patients and medications can differ between ICUs and this could lead to different needs for pDDI alerts. We hypothesize that such local limited tweaking will rarely happen but can positively influence system acceptance [30].

**Fig. 3 Fig3:**
[figure not shown]
Timeline of stepped-wedge trial

### Study outcomes

The primary outcome of this study is the incidence of clinically relevant pDDIs per 1000 medication administrations. To be able to compare our results to other studies, we also defined secondary outcomes. These are the number of pDDIs per patient, the number of clinically relevant pDDIs per patient, the proportion of patients admitted to the ICU with at least one pDDI, and the proportion with at least one clinically relevant pDDI [9]. Other secondary outcomes are ICU length of stay, the override rate of clinically relevant pDDI alerts and the number of ADEs related to DDIs per 1000 medication administrations. In Table 1 definitions of study outcomes are described. These definitions are in line with previous studies [5, 8].

**Table 1 Tab1:** Overview of study outcomes

Study outcomes	Definition
pDDI	Two potentially interacting medications administered concomitantly which could result in an actual DDI.
Clinically relevant pDDI	A pDDI considered clinically relevant for the ICU setting, according to the results from our Delphi procedure.
ADE related to DDI	A DDI that resulted in patient harm.
Appropriately handled pDDI	Two potentially interacting medications were administered concomitantly (pDDI), but there is evidence that adequate measures were taken to prevent patient harm or diminish the risk of patient harm.

In addition, we will also measure the proportion of appropriately handled clinically relevant pDDIs. This is an important outcome, specifically in the ICU setting, where the patient is in a critical condition and sometimes the risk of prescribing interacting medications is subject to the need for treatment [17]. Furthermore, if prescribing a pDDI cannot be averted, there are several management strategies to keep the potential harm to a minimum. Management strategies include for example monitoring laboratory values such as creatinine, potassium, therapeutic drug monitoring and adjustment of medication dosage [8]. Because of this, it is not only important to know whether a reduction in the number of clinically relevant pDDIs has occurred, it is also important to know how many pDDIs occurred that were handled appropriately, for example by conducting therapeutic drug monitoring.

To assess whether a clinically relevant pDDI alert is handled appropriately or not, for each clinically relevant pDDI we will list the possible management strategies based on the recommendations available in the G-standard. A pDDI will be considered as handled appropriately if there is ‘evidence in the data’ that one or more of the defined management strategies has been implemented based on medication, laboratory and ECG data of the patient.

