### Establishing clinically relevant pDDIs

To determine which pDDIs are clinically relevant for the ICU setting, we will apply a modified Delphi procedure, in which an expert panel of intensivists and hospital pharmacists will assess the clinical relevance of pDDIs. The pDDIs to be assessed will be selected from the G-standard according to their frequency in the ICU and the assigned severity level. In essence, a pDDI is defined as clinically relevant for the ICU setting when non-standard monitoring for possible pDDI effects is required, or the pDDI should always be avoided. The modified Delphi procedure will be based on the RAND method [29], and will consist of an online questionnaire and expert panel meeting.

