### Intervention

Our intervention consists of a version of the MiM that will only provide alerts for pDDIs considered clinically relevant in the ICU, according to our Delphi procedure. pDDI alerts considered not clinically relevant for the ICU will be turned off. This MiM version tailored to the ICU setting will be called MiM+. Our hypothesis is that alert fatigue can be reduced by MIM+, as the set of pDDIs for which alerts are provided at the point of prescribing, will be restricted and more specific for the ICU setting.

In the four participating ICUs that do not use the current MIM CDSS for pDDIs, the MiM+ software will be installed. Duplicate order alerts will not be shown in these four ICUs.

In the five ICUs that already use MiM as CDSS for pDDIs, MiM+ will start operating in these ICUs during the intervention phase. However, pDDI alerts not assessed during our Delphi procedure and for which an ICU gets alerts according to its current alert level setting, will not be changed. Furthermore, other types of alerts such as duplicate order alerts will also not be changed by our intervention. In short, the ICUs with a MiM CDSS will experience change in the alerts that were assessed in the Delphi rounds, in the sense that alerts for the pDDIs deemed irrelevant will be suppressed. All participating ICUs will receive an on-site training for the prescribing physicians about MiM+ given by a researcher involved in this study.

Apart from this intervention, all participating ICUs will receive two performance feedback rapports before MiM+ implementation. In these reports, results of a retrospective analysis of medication administration data on the occurrence of pDDIs will be included. The results will include pDDI occurrence over one year for the specific ICU, benchmarked against the other participating ICUs.

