### Data collection

To assess the effect of our intervention on the primary and secondary outcomes, and to gain insight in pDDI type and occurrence for the purposes of our Delphi procedure, we will use routinely recorded data extracted from MetaVision ICU, MiM/MiM+, and the NICE registry.

Data covering all ICU admissions in the period from at least one month prior to the MIM+ implementation up to one month after the intervention period will be extracted. All data from Metavision ICU and MiM/MiM+ will be collected at the patient level using a coded admission number of the patient as an identifier. This coded admission number cannot be used to identify a specific patient. The following routinely recorded data from Metavision ICU will be extracted: medication orders, orders for an electrocardiogram (ECG) and laboratory orders. Medication orders will include the name of the ordered medication, generic product code of the medication, dosage and frequency, validation of the order indicating whether the medication order was actually administered, the start and end time of the order, and whether or not the order was cancelled. In MetaVision ICU, each administration is registered separately. These data are necessary to assess the primary outcome: the occurrence of clinically relevant pDDIs per 1000 medication administrations. Laboratory orders will include name of test ordered, date and time of the order, and for results of the test. ECG orders will include date and time of the order. ECG and laboratory data together with medication data are necessary to assess if, following a pDDI alert, appropriate management strategies were employed (secondary outcome: appropriately handled clinically relevant pDDIs) and to assess whether ADEs occurred (secondary outcome: number of ADEs related to DDIs per 1000 medication administrations).

The following routinely recorded data from MiM and subsequently MiM+ will be extracted: all (clinically relevant) pDDI alerts that were produced, date and time of the alert, which medication (name and generic product code) was involved, if the alert was overridden or not, and if entered by the user, the reason for overriding the alert. These data are necessary to assess the secondary outcome: override rate of (clinically relevant) pDDI alerts per 1000 medication administrations.

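### The handling outcome is a proportion of the interactions that still occur, so it can shift between conditions without any change in handling; an unhandled-pDDI rate should stand beside it

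*Protocol article*

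**What the plan says.** All places are in the protocol article, Methods/design.

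- **Primary outcome** (Study outcomes): "The primary outcome of this study is the incidence of clinically relevant pDDIs per 1000 medication administrations". Under Data collection, the detection algorithm uses only orders that were administered, so every co-administered relevant pair counts, handled or not.
- **Clinical relevance** (Establishing clinically relevant pDDIs): a pair qualifies "when non-standard monitoring for possible pDDI effects is required, or the pDDI should always be avoided". For part of the list, then, extra monitoring is an accepted response.
- **Handling outcome** (Study outcomes): "we will also measure the proportion of appropriately handled clinically relevant pDDIs". Table 1 describes the handled case as "Two potentially interacting medications were administered concomitantly (pDDI), but there is evidence that adequate measures were taken". The criterion stated below the table asks for a trace in the records "that one or more of the defined management strategies has been implemented based on medication, laboratory and ECG data of the patient".
- **Purpose of that outcome** (Study outcomes): a fall in the number of pDDIs is said not to be enough, and "it is also important to know how many pDDIs occurred that were handled appropriately".
- **Unit**: Table 1 and the operative criterion refer to the pDDI. The sentence introducing the criterion speaks of an alert being handled, and Data collection says the laboratory and ECG data serve "to assess if, following a pDDI alert, appropriate management strategies were employed".
- **Control condition** (Intervention): "In the four participating ICUs that do not use the current MIM CDSS for pDDIs, the MiM+ software will be installed". Those four units have no MiM alerts before their switch.

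**The concern.** The proportion is conditional on an event that happens after the switch and that the intervention is designed to make rarer. Randomising the order of the ICUs does not make the remaining pDDIs in the two conditions alike. If MiM+ mainly averts pairs that would have gone unmonitored, the proportion handled rises; if it mainly averts pairs that would have been monitored anyway, it falls. Neither movement says anything about how the remaining pairs were managed.

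This matters because the handling outcome carries evidence that the primary outcome cannot. Where a prescriber answers an alert by monitoring and keeps both drugs, the primary count does not move. A reader of the results would turn to the handling outcome to see that response, and would find a measure whose comparison between conditions mixes handling with selection.

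The wording on the unit adds a smaller difficulty. If handling were assessed only after an alert, four ICUs would contribute nothing in their control months. In the other five, the control-month alerts would depend on the severity level that each unit sets for itself (Study setting).

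**Working it through.** **1. The plan's own figure.** Inputs from Sample size: 9 clusters (I), 10 periods (T), one cluster switching per step, 600 administrations per cluster-period, rates 0.0420 and 0.0336, ICC 0.12, Poisson variance, two-sided Wald test at 0.05. The Hussey-Hughes variance is

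Var = I·s²(s² + T·τ²) / [(I·U − W)s² + (U² + I·T·U − T·W − I·V)τ²],

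with U = 45 and W = V = 285, so the bracketed constants are 405 − 285 = 120 and 2025 + 4050 − 2850 − 2565 = 660.

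- Mean rate 0.0378: s² = 0.0378/600 = 0.000063 and τ² = (0.12/0.88) × 0.0378 = 0.00515.
- SE = 0.00293; 0.0084/0.00293 = 2.87; power 81.8%.
- Taking the control rate as total variance instead gives 82.6%.

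Both agree with the stated 83%. That figure describes avoidance only. If half of a 20% response were avoidance (42.0 to 37.8), power on the primary outcome would be about 29%; at three quarters (42.0 to 35.7), about 56%. Those splits are assumptions.

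**2. The proportion with handling held fixed.** Planned rates: 42.0 to 33.6, so 8.4 per 1000 are averted. Assumed: 50% handled in control, that is 21.0 handled and 21.0 unhandled. In the two-type rows each type contributes 21.0 per 1000.

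| Which 8.4 are averted | Handled after | Proportion handled | Unhandled per 1000 |
|---|---|---|---|
| Control, for reference | 21.0 | 50.0% | 21.0 |
| Handling-neutral sample | 16.8 | 16.8/33.6 = 50.0% | 16.8 |
| Types 60%/40%, all from the 40% type | 21 × 0.6 + 12.6 × 0.4 = 17.64 | 52.5% | 15.96 |
| Types 60%/40%, all from the 60% type | 12.6 × 0.6 + 21 × 0.4 = 15.96 | 47.5% | 17.64 |
| Types 80%/20%, all from the 20% type | 21 × 0.8 + 12.6 × 0.2 = 19.32 | 57.5% | 14.28 |
| Types 80%/20%, all from the 80% type | 12.6 × 0.8 + 21 × 0.2 = 14.28 | 42.5% | 19.32 |
| Extreme: all would have been unhandled | 21.0 | 21/33.6 = 62.5% | 12.6 |
| Extreme: all would have been handled | 12.6 | 12.6/33.6 = 37.5% | 21.0 |

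If the 80% type makes up 30% of pDDIs, the baseline is (12.6 × 0.8 + 29.4 × 0.2)/42 = 38.0%. Averting only that type gives (4.2 × 0.8 + 29.4 × 0.2)/33.6 = 27.5%, a shift of −10.5 points. At a 70% share, averting only the other type moves 62.0% to (29.4 × 0.8 + 4.2 × 0.2)/33.6 = 72.5%, a shift of +10.5 points.

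**3. A monitoring-only response.** All 42.0 pairs continue and 8.4 more are monitored: handled 29.4 (70%), unhandled 12.6. The primary rate ratio is 1.0, while the unhandled rate falls by (21.0 − 12.6)/21.0 = 40%.

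**4. What the unhandled rate can and cannot show.** In aggregate it equals the primary rate × (1 − proportion handled), for example 33.6 × (1 − 0.625) = 12.6. It reads 12.6 both when 8.4 unhandled pairs are averted and when 8.4 more pairs are monitored. In the neutral row it falls from 21.0 to 16.8 with handling unchanged. It is a composite of avoidance and handling.

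**The case against.** The strongest reply is that the protocol has thought about this. Its stated aim is prevention, which the primary outcome measures. It says openly that some pDDIs cannot be averted, and it adds the handling outcome for that reason. It also lists ADEs related to DDIs per 1000 administrations, which is not conditional on the pDDIs that remain and can reflect both avoidance and monitoring. All of this stands. A reader might infer that the primary outcome is wrong or that the stated power is in error; the documents support neither.

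A reader might also infer that the proportion should be dropped in favour of the unhandled rate. That does not follow. In the neutral case the proportion correctly stays at 50%, while the unhandled rate falls because of avoidance alone. Each measure answers a question the other does not.

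Third, the unhandled rate can be derived from two planned results, and the sentence on how many pDDIs were handled leaves room for a count. That is fair, but a figure derived afterwards has no named status and no planned modelled comparison.

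Finally, the alert wording might be read as fixing an alert-only denominator. Table 1 and the operative criterion use administered pairs, and the detection algorithm needs no alert, so this is loose wording to be aligned and does not establish such a denominator.

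**Conclusion.** The point holds in a limited form. The handling proportion is conditional on pDDIs that still occur after the switch, so comparing it between conditions is safe only if averted pDDIs are handling-neutral, and nothing in the article supports that assumption. With 50% handled in control and the planned 20% reduction, the artefact is zero in the neutral case, 7.5 points either way for two equal types handled 80% and 20%, and 12.5 points at the extremes. The extremes require every averted pair to come from one handling group and should not be read as expected values. Handling rates and type mix are assumptions throughout, so neither the size nor the sign in this trial can be known from the documents.

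It would also go too far to say that a fully effective monitoring alert must leave the primary outcome unchanged, since some prescribers may answer such an alert by avoiding the pair. What can be said is that the primary outcome gives no credit to the monitoring response itself, and that the handling measure added for that purpose does not allow a clean comparison.

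**What to change.** - Add a named secondary outcome beside the proportion: clinically relevant pDDIs not appropriately handled per 1000 medication administrations. Compute it on all administered pairs in both conditions, whether or not an alert fired, and analyse it with the primary model.
- Describe it as a composite of avoidance and handling. Keep the proportion, and interpret it as conditional on the pDDIs that occurred.
- Reconcile the alert-based wording below Table 1 and under Data collection with the definition in Table 1, because four ICUs have no MiM alerts before MiM+.

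No new data are needed: the medication, laboratory and ECG records are already to be extracted, and the denominator is that of the primary outcome. The cost is one more secondary outcome to report. The primary outcome and the sample size stay as they are.

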### Data collection

To assess the effect of our intervention on the primary and secondary outcomes, and to gain insight in pDDI type and occurrence for the purposes of our Delphi procedure, we will use routinely recorded data extracted from MetaVision ICU, MiM/MiM+, and the NICE registry.

Data covering all ICU admissions in the period from at least one month prior to the MIM+ implementation up to one month after the intervention period will be extracted. All data from Metavision ICU and MiM/MiM+ will be collected at the patient level using a coded admission number of the patient as an identifier. This coded admission number cannot be used to identify a specific patient. The following routinely recorded data from Metavision ICU will be extracted: medication orders, orders for an electrocardiogram (ECG) and laboratory orders. Medication orders will include the name of the ordered medication, generic product code of the medication, dosage and frequency, validation of the order indicating whether the medication order was actually administered, the start and end time of the order, and whether or not the order was cancelled. In MetaVision ICU, each administration is registered separately. These data are necessary to assess the primary outcome: the occurrence of clinically relevant pDDIs per 1000 medication administrations. Laboratory orders will include name of test ordered, date and time of the order, and for results of the test. ECG orders will include date and time of the order. ECG and laboratory data together with medication data are necessary to assess if, following a pDDI alert, appropriate management strategies were employed (secondary outcome: appropriately handled clinically relevant pDDIs) and to assess whether ADEs occurred (secondary outcome: number of ADEs related to DDIs per 1000 medication administrations).

The following routinely recorded data from MiM and subsequently MiM+ will be extracted: all (clinically relevant) pDDI alerts that were produced, date and time of the alert, which medication (name and generic product code) was involved, if the alert was overridden or not, and if entered by the user, the reason for overriding the alert. These data are necessary to assess the secondary outcome: override rate of (clinically relevant) pDDI alerts per 1000 medication administrations.

To detect (clinically relevant) pDDIs in the medication orders data, we will develop a computerized algorithm based on the pDDI rules from the G-standard. This algorithm will then be applied to medication order data from the participating ICUs. Only validated medication orders, i.e. medication orders that were actually administered, will be considered. In addition, each separate administration for a specific drug will be attributed to one composite medication administration if the time gap between separate administrations does not exceed a specific amount of time, such as 24 h (regardless of the route of administration).

A second developer will validate the algorithm. To assess the number of ADEs related to DDIs per 1000 medication administrations, we will develop computerized ADE triggers. Triggers are sentinel words or events that may point to the occurrence of an ADE, such as increased or decreased laboratory values, ordering an ECG or prescribing an antidote [31]. The triggers that we develop and ADEs identified by these triggers will be published along with the results of this study.

In addition to data from Metavision ICU and MiM/MiM+, we will also use data submitted to the NICE registry by the participating ICUs. These data include clinical, physiological and demographic data required to calculate outcomes such as ICU length of stay, hospital length of stay, hospital mortality, and expected mortality based on disease severity predicted from clinical data of the first 24 h of ICU admission [27]. Data from Metavision ICU, MiM/MiM+ can be linked with NICE registry data using the earlier mentioned unique coded admission number.

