## Background

Drug-drug interactions (DDIs) are an important cause of adverse drug events (ADEs) [1]. In ICU patients, approximately 16% of all ADEs are caused by a DDI [2]. ADEs in the ICU are linked to increased length of stay, higher morbidity and mortality and increased hospital costs [3]. A DDI occurs when one or more drugs affect the pharmacokinetics (the body’s effect on the drug) and/or pharmacodynamics (the drug’s effect on the body) of one or more other drugs [4]. In the ICU, between 46 and 90% of the patients are exposed to a potential DDI (pDDI) [5]. This rate is twice as high compared to patients on general wards [6, 7]. A pDDI is defined as two potentially interacting medications administered concomitantly [8]. A pDDI may lead to an actual DDI, which could result in an ADE.

Studies have demonstrated the potential of clinical decision support systems (CDSSs) in preventing pDDIs [9, 10]. CDSSs focus on helping clinicians to improve their clinical performance. Computerized clinical decision support is defined as “providing clinicians or patients with computer-generated clinical knowledge and patient-related information, intelligently filtered or presented at appropriate times, to enhance patient care” [11]. A CDSS provides guidance at the point of prescribing by means of usually interruptive medication alerts that warn the prescriber for risky situations such as pDDIs [10]. However, the literature shows that there is considerable room for improvement, especially regarding the clinical relevance (and thereby the specificity) of the medication alerts generated by CDSSs [12–14]. Which pDDI alerts are generated by a CDSS depends on the underlying (sometimes commercial) knowledge base. [15] Lack of a fit between the clinical setting and the pDDI knowledge base used can be a cause of low specificity of medication alerts. Low specificity leads to alert fatigue and a high override rate of alerts. [16] Studies show that clinicians override alerts, including pDDI alerts, in 49 to 96% of the cases [16, 17]. These “side effects” of CDSS diminish the potential value of CDSSs for medication safety.

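### The override outcome is worded per 1000 administrations, so it moves with the number of alerts: four ICUs start at zero by construction, and the alert set is left open

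*Protocol article*

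**What the plan says.** The protocol article refers to overriding in three ways.

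- **Background** uses it per alert: "clinicians override alerts, including pDDI alerts, in 49 to 96% of the cases".
- **Study outcomes** lists "the override rate of clinically relevant pDDI alerts and the number of ADEs related to DDIs per 1000 medication administrations". The alert set is the clinically relevant one. The words about 1000 administrations attach clearly only to the ADE count, and Table 1 does not define the override rate.
- **Data collection** states it as the "override rate of (clinically relevant) pDDI alerts per 1000 medication administrations". Here administrations are the denominator, and the brackets leave open whether all pDDI alerts or only the relevant ones count.

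The same section extracts from the alert log "all (clinically relevant) pDDI alerts that were produced, date and time of the alert", together with whether each alert was overridden.

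On the intervention, five of the nine ICUs already use MiM and four do not (Study setting). In the five, the Intervention section says that "alerts for the pDDIs deemed irrelevant will be suppressed". In the four, MiM+ is newly installed. Stepped-wedge design implementation lets an ICU add or discard a pDDI alert during its pilot month.

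**The concern.** The Theoretical foundation section makes overriding a link in the trial's argument: more specific alerts, less fatigue, fewer overrides, fewer pDDIs. Testing that link requires the probability that a fired alert is overridden. A rate per 1000 administrations is that probability multiplied by how often alerts fire, and the intervention changes how often alerts fire.

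The outcome can therefore move when prescribers behave exactly as before. In the four ICUs without MiM it goes from zero to some positive value once alerts exist. Read at face value, that would suggest more overriding after an intervention meant to reduce it. The alert set also differs between the two sections that name the outcome, and that choice decides whether suppression in the other five ICUs affects the figure at all.

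**Working it through.** **The plan's own figures.** The article gives no figure for the override rate. Its only design calculation concerns the primary outcome: 42.0 × 0.80 = 33.6 pDDIs per 1000 administrations, with a stated power of 83%. I rebuilt this with the Hussey-Hughes variance, using 9 clusters, 10 periods, 600 administrations per cluster-period and ICC 0.12. The residual variance was the mean Poisson rate, (0.042 + 0.0336)/2 = 0.0378, and the between-cluster variance was (0.12/0.88) × 0.0378. Power comes to 81.8%, or 83.2% with a binomial variance. The stated figure is reproduced within about a point, and the override outcome plays no part in it.

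**Formula.** Overrides per 1000 administrations = A × p, where A is alerts fired per 1000 administrations and p is the probability that an alert is overridden. Unchanged behaviour means that p is fixed.

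**Inputs**

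- p = 0.49 and 0.96, the ends of the range in the Background.
- R = 42 relevant alerts per 1000 administrations. This takes the event rate in Sample size and assumes one alert per relevant pDDI. The relative changes below do not depend on R.
- All pDDI alerts in a MiM ICU before MiM+ = k × R, with k = 1.5, 2 or 3. The article gives no figure, so k is an assumption. It also assumes that everything beyond R is suppressed. Alerts not assessed in the Delphi procedure stay on, so the real fall for a given k would be smaller.
- The same p for every alert.

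**Results with p unchanged (per 1000 administrations)**

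| Setting | p = 0.49 | p = 0.96 | Change |
|---|---|---|---|
| Four ICUs without MiM, either alert set | 0 → 20.6 | 0 → 40.3 | from zero |
| Five MiM ICUs, relevant alerts only | 20.6 → 20.6 | 40.3 → 40.3 | none |
| Five MiM ICUs, all pDDI alerts, k = 2 | 41.2 → 20.6 | 80.6 → 40.3 | −50% |
| Nine ICUs, equal weight, relevant only | 11.4 → 20.6 | 22.4 → 40.3 | +80% |

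- Row 1: 42 × 0.49 = 20.6 and 42 × 0.96 = 40.3.
- Row 3: the fall is 1 − 1/k, which is 33%, 50% or 67% for k = 1.5, 2 or 3.
- Row 4: before MiM+, only five of nine ICUs contribute, giving (5/9) × R × p; afterwards all nine give R × p. The ratio is 9/5.

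If all pDDI alerts were counted across nine ICUs, the after-to-before ratio would be 9/(5k): 1.2 for k = 1.5, 0.9 for k = 2 and 0.6 for k = 3. The direction would then depend on the assumed alert mix, with p constant throughout. These nine-ICU figures are simple before-and-after averages, not a fitted stepped-wedge model.

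**Per alert instead.** Overridden relevant alerts divided by relevant alerts fired equals p before and after in the five MiM ICUs (0.49 and 0.49, or 0.96 and 0.96). In the other four the control value is 0/0, so it does not exist.

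**The case against.** The strongest reply starts from Study outcomes, which names "the override rate of clinically relevant pDDI alerts". The Intervention section suppresses only alerts judged irrelevant, so those alerts were never in that numerator and switching them off cannot lower it. This stands. The exception is a relevant alert discarded in the pilot month, and the article expects such local changes to be rare.

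A reader might nevertheless infer from "pDDI alerts considered not clinically relevant for the ICU will be turned off" that the outcome must fall in the MiM ICUs whatever is counted, or that a nine-ICU analysis necessarily mixes two artefacts of opposite sign. The article does not support either inference. Both need all pDDI alerts to be counted, which only the brackets in Data collection permit.

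Three further objections have weight:

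- **The denominator is not settled.** It is stated once, in Data collection, and not clearly in Study outcomes. So the defect is partly an inconsistency. But the one explicit wording is the misleading one, so this is more than missing detail.
- **No pooled analysis of this outcome is described.** The model in Statistical analysis is stated for pDDIs per 1000 administrations, and how the override rate is compared may be left to an analysis plan that is not shown. The 80% is therefore conditional on a nine-ICU comparison.
- **Changing the denominator does not give the four ICUs a control value.** True, but a missing value is visible, whereas a zero enters an analysis as if it had been observed. Previous MiM use is a candidate covariate, but a main effect would not remove a zero confined to the control phase of four clusters.

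It would also go too far to say that the rate measures alert volume alone. It is a product, and behaviour still moves it.

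**Conclusion.** The concern holds in a limited form. As worded in Data collection, the override outcome combines alert volume with prescriber behaviour, and it disagrees with the per-alert use in the Background. Study outcomes and Data collection need to be reconciled on both denominator and alert set.

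- **Four ICUs without MiM:** the control value is zero by construction on either alert set. This depends only on their having no MiM alerts before MiM+.
- **Nine ICUs with equal weight, relevant alerts only:** an 80% rise with unchanged behaviour, if such a comparison is made.
- **Five MiM ICUs:** no mechanical change for relevant alerts, pilot-month discards aside. A fall of 33% to 67% follows only if all pDDI alerts are counted, and its size rests on the assumed k and on full suppression of the rest.

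This is one secondary outcome. It should be corrected because it bears on the mechanism the trial proposes, but the primary outcome and its power are untouched.

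**What to change.** - In both Study outcomes and Data collection, define the outcome as overridden clinically relevant alerts divided by clinically relevant alerts fired.
- Compare control with MiM+ only in the five MiM ICUs, on Delphi-relevant pairs that their control-period settings already alerted on. Each ICU sets its own alert level, so this keeps the alert set the same in both phases. Fixing the set matters even per alert: over all pDDI alerts, the proportion would shift with alert mix if irrelevant alerts are overridden more often.
- Report the four other ICUs descriptively, and state that they have no control-period value.
- Report alert volume per 1000 administrations as a separate descriptive measure.

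The cost is a change of wording, denominator and analysis set. Every alert and its override status are already extracted, so no new data are needed. The price is precision, because the comparison rests on five ICUs.
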